### Adverse events

3.5

During the trial, the adverse reactions such as palpitations, sweating, pallor, dyspnea, and blood oxygen saturation lower than 85% will be accurately recorded. Once there are adverse reactions, patients should be stopped immediately and have a bed rest. Researchers need to observe closely the condition, and report to the doctor in time. The doctor will judge the degree of the adverse events initially and its correlation with the experimental intervention, thus give further treatment suggestions. At the same time, researchers should also make detailed records, such as the degree, time, treatment measures, and outcome of adverse events.

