Liuzijue, a kind of traditional Chinese Qigong, emphasizes the integration of body adjustment, breath adjustment, and heart adjustment in the process of exercise.^[10]^ Liuzijue adopts reverse abdominal breathing, mouth exhale, and nose inhale to match the action. At the same time, emphasizes the role of spirit and ideas. When exhaling, concentrate and think about the viscera corresponding to each word. The 6 sounds of “xu,” “he,” “hu,” “si,” “chui,” and “xi” in Liuzijue correspond to lung, heart, spleen, liver, kidney, and Sanjiao respectively. Respiratory muscles such as intercostal muscle, rectus abdominis muscle, and pectoralis major muscle are mobilized to participate in training so as to deepen respiratory depth and improve pulmonary ventilation.^[11]^ A large number of studies have confirmed that Liuzijue can improve lung function, dyspnea symptoms, exercise endurance, and quality of life in stable COPD patients.^[11–13]^

However, AECOPD patients often have severe dyspnea, respiratory muscle fatigue and respiratory acidosis during hospitalization, so they need to be treated with non-invasive ventilation (NIV).^[14]^ On the other hand, nutrition level and hormone medication will cause patients to feel tired. At the same time, they are also worried that getting out of bed will aggravate their illness.^[15,16]^ Thus AECOPD patients have poor compliance with getting out of bed at the early stage, especially those with NIV. Therefore, it is particularly urgent to explore an effective exercise method suitable for AECOPD patients with NIV. Sitting and lying Liuzijue is a kind of medium and low intensity aerobic exercise which is on the basis of Liuzijue. It is suitable for people who are too old and frail to stand for a long time. Compared with the standing Liuzijue, it is more appropriate for long-term bedridden AECOPD patients with NIV.

Therefore, in this study, sitting and lying Liuzijue will be used to carry out early pulmonary rehabilitation exercise in AECOPD patients with NIV. The purpose of this study is to evaluate the effect of sitting and lying Liuzijue on blood gas index, pulmonary function, dyspnea symptoms, exercise endurance, BODE index, anxiety and depression, and quality of life. Thus, to provide a safe, effective, and good compliance method of TCM pulmonary rehabilitation exercise for AECOPD patients with NIV.

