### The experimental group

3.2

On the basis of the control group, participants in the experimental group will practice sitting and lying Liuzijue once every morning and evening, 30 minutes each time, for a total of 3 months. Before the official start of the experiment, 2 members of the research group need to be trained in skills and methods. After successfully passing the examination, they would conduct action guidance and training to the participants. The teaching time of patients should be controlled within 5 days, and they should be assessed on the last day. After the patients have correctly mastered the steps, essentials and matters needing attention of sitting and lying Liuzijue, they will formally enter the experiment.

Sitting and lying Liuzijue exercise begin immediately after the appearance of the lung infection control window. Exercise once every morning and evening, each time for 30 minutes, for a total of 3 months. In the process of exercise, the participants need to take off the NIV mask and use nasal catheters to inhale oxygen. The pulse oxygen saturation meter will be used to closely monitor the changes of heart rate and fingertip oxygen saturation. Take continuous exercise and intermittent exercise according to the tolerance of participants. The next day, ask the participants about their physical recovery and observe their breathing and heart rate during the entire exercise to confirm whether the current exercise intensity is appropriate.

All participants use reverse abdominal breathing, exhale first and then inhale. Read when they exhale, lift the anus and contract the kidney at the same time (abdomen and buttocks, urethral orifice, and anal micro-lift). When inhaling, the lips are gently closed, the tongue is against the upper jaw, the whole body is relaxed, the lower abdomen is naturally raised, and the air is naturally inhaled. After reading each word 6 times, using natural breathing, tongue against the palate (cis-abdominal breathing can also be used). The function is to adjust breathing, restore nature, and take a short rest. The detailed steps are shown in Fig. 3.

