**Figure 3 F3:**
[figure not shown]
Main characteristics of sitting and lying Liuzijue.

When the participant is discharged from the hospital, we will distribute sitting and lying Liuzijue exercise manual, video, and intervention diary. At the same time, communicate, guide, and supervise through telephone and WeChat groups.

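### Adverse events are likely to be found unequally in the two arms, mainly after discharge, so a comparative safety conclusion would not be well supported

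*Protocol article*

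**What the plan says.** Section 3.5 covers the whole trial, names no arm and gives an open list of examples: "During the trial, the adverse reactions such as palpitations, sweating, pallor, dyspnea, and blood oxygen saturation lower than 85% will be accurately recorded". The response is "Once there are adverse reactions, patients should be stopped immediately and have a bed rest". On causality: "The doctor will judge the degree of the adverse events initially and its correlation with the experimental intervention".

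The monitoring by the research team is set out in section 3.2 (The experimental group). For the sessions: "The pulse oxygen saturation meter will be used to closely monitor the changes of heart rate and fingertip oxygen saturation". For follow-up of each session: "The next day, ask the participants about their physical recovery and observe their breathing and heart rate during the entire exercise". The schedule is "Exercise once every morning and evening, each time for 30 minutes, for a total of 3 months". After Figure 3 the same section adds: "When the participant is discharged from the hospital, we will distribute sitting and lying Liuzijue exercise manual, video, and intervention diary", with guidance and supervision by telephone and WeChat. Section 3.3 (Compliance) repeats this contact. It speaks of participants without naming an arm, but its subject is keeping up Liuzijue practice.

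Section 3.1 (The control group) describes the routine care that section 3 gives to both arms. It includes nursing observation, oxygen saturation kept at 90% to 94%, and breathing exercises. Section 3.4 (Outcome measures) places the outcome assessment at week 13.

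The Introduction gives the wider purpose: "to provide a safe, effective, and good compliance method of TCM pulmonary rehabilitation exercise for AECOPD patients with NIV".

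**The concern.** The number of adverse events recorded in an arm depends on how many occur and on how hard anyone looks. Here the active looking is described for one arm. A count by arm would then mix the effect of the exercise with the effect of surveillance, and the two could not be separated afterwards.

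If controls' events are missed, the exercise arm looks worse than it is. A real reduction in exacerbations or readmissions could be hidden in the same way. Conversely, a quiet record from supervised sessions says nothing about whether exercise patients did better or worse than controls over the three months. The question is not trivial in this trial: the patients are recovering from an exacerbation that needed NIV, and the article hopes to offer a safe method.

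**Working it through.** The article states no adverse-event rate, safety margin or safety power, so there is no figure to reproduce. The check is a comparison of the text by phase and arm, followed by an illustration.

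**1. What is described, by phase and arm**

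| Phase | Exercise arm | Control arm |
|---|---|---|
| In hospital | Routine observation and saturation control (3.1), plus session oximetry and heart rate, next-day questions (3.2) and daily supervision (3.3) | Routine observation and saturation control (3.1) |
| Discharge to week 13 | Diary, telephone, WeChat (3.2, 3.3) | No trial contact described |
| Week 13 | Outcome assessment (3.4) | Outcome assessment (3.4) |

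In hospital the difference is one of degree. After discharge it is contact against none described.

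**2. How long each phase lasts**

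The article gives no length of stay. Counting 13 weeks from the start of the intervention gives 13 × 7 = 91 days. The phase after discharge is the longer one unless the remaining stay exceeds 91 / 2 ≈ 45 days. Over about 90 days, two sessions a day come to 2 × 90 = 180 sessions per exercise patient.

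**3. The wording of section 3.5**

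The time window and the open list are neutral between arms. Two elements are not. To stop a patient presupposes an activity in progress, and a causality judgement against the experimental intervention has no counterpart for a control patient. Nothing states that events are sought in the same way or on the same schedule in both arms.

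**4. What unequal detection could do (illustration)**

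Inputs: n = 32 per arm (section 2.3) and two-sided 5% tests (section 3.6). Two inputs are assumptions: the true event rate p, equal in both arms, and the fraction c of controls' events that are caught, with all events caught in the exercise arm. The observed rates are then p1 = p and p2 = c·p.

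Formula (normal approximation), with m = (p1 + p2)/2:

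P(false difference) ≈ Φ{[(p1 − p2) − 1.96·√(2m(1 − m)/n)] / √([p1(1 − p1) + p2(1 − p2)]/n)}

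Example with p = 0.20 and c = 0.5:
- p1 = 0.20, p2 = 0.10, m = 0.15
- √(2 × 0.15 × 0.85/32) = 0.0893, times 1.96 = 0.175
- √((0.16 + 0.09)/32) = 0.0884
- (0.10 − 0.175)/0.0884 = −0.85, so Φ ≈ 0.20

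| True rate, both arms | Controls' events caught | Observed rates | False difference at 5% |
|---|---|---|---|
| 20% | half | 20% v 10% | about 20% |
| 20% | a quarter | 20% v 5% | about 44% |
| 40% | half | 40% v 20% | about 41% |
| 40% | a quarter | 40% v 10% | about 81% |

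With equal detection the figure would be about 5%. Fisher's exact test, which section 3.6 also allows, is more conservative and would give lower figures. The shift in the observed rates would be the same whichever test is used, or with no test at all.

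**The case against.** The strongest reply is that section 3.5 is neutral on its face: it runs for the whole trial, names no arm and gives only examples. Safety is neither a primary nor a secondary outcome, and no between-arm test of adverse events is specified. The article is also condensed, so a full procedure covering both arms may exist elsewhere. All of this is correct, and it limits the point.

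A reader might infer any of the following. The document does not support them:

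- **That adverse events are defined as reactions during exercise sessions.** The response and the causality question lean that way, but the definition does not.
- **That events are ascertained almost only in the exercise arm.** In hospital, controls have nursing observation and a saturation range to be held, so a marked desaturation should not go unseen.
- **That death, readmission, a new exacerbation or a return to ventilation would go unrecorded.** The list is open, and section 2.4.4 names serious acute illness among the termination and withdrawal criteria for all participants. Detailed forms may stand in the full protocol.
- **That the trial can say nothing about safety.** How well the sessions were tolerated in the exercise arm can be described from what is planned.
- **That the upper limit of 8.9% for zero events in 32 patients measures the problem.** It equals 1 − 0.05^(1/32), which reflects only the sample size and would be the same with perfectly equal detection.

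What remains is that the article does set out an event procedure, and what it sets out is lopsided. The response and causality are tied to the exercise, and active follow-up is described for one arm.

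**Conclusion.** The point holds in a limited form. Followed as written, the plan is likely to find events unequally, modestly in hospital and clearly between discharge and week 13. A conclusion that the exercise is as safe as, or safer or less safe than, routine care would not be well supported. A description of session tolerability in the exercise arm would be.

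The size cannot be derived from the document. The range of about 20% to 81% for a false difference rests entirely on the assumed event rates and detection fractions, and on a between-arm test that the article does not specify for adverse events. It shows that plausible gaps in detection matter at this sample size and does not predict the result. The conclusion also assumes that no equal enquiry in both arms is laid down in a fuller document. If one is, a sentence saying so would settle the matter.

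**What to change.** 1. At the existing week-13 contact, ask every participant in both arms the same fixed list of memorable events over the same period from randomisation: death, readmission, new exacerbation, return to ventilation. For participants who died or were lost, use hospital records or family.
2. Summarise these events by randomised group.
3. Report reactions during sessions, including transient symptoms and desaturation, separately, for the exercise arm only and with no between-arm test.
4. State as a limitation that the exercise arm keeps more contact through the diary, calls and WeChat.

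The cost is one short form at a contact already planned and a few lines of text. The downsides are reliance on recall over 13 weeks, which is why transient symptoms such as pallor or sweating are left out of the common list, and some inequality of contact that one form cannot remove. Nothing in the treatment, the monitoring or the handling of a reaction needs to change for this.

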### Statistical analysis

3.6

Two researchers who are not be involved in the recruitment, evaluation, or training of patient will be responsible for entering the data. Statistical analysis will be carried out by using SPSS 24.0 statistical software. If the measurement data accorded with normal distribution, it will be described by mean and standard deviation. If not, it will be described by median and quartile distance. The measurement data will be examined using group *t* tests or non-parametric tests, the count data will be tested using a Chi-square test or Fisher exact probability method, and the grade data will be tested using non-parametric tests. All statistical tests will be bilateral tests and *P* < .05 will be considered to indicate statistical significance.

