### Design

2.1

This study is a clinical randomized controlled trial. Sixty four AECOPD participants with NIV will be conducted in the Hospital of Chengdu University of TCM (Chengdu, China). Participants will be recruited through a recommendation by the respiratory clinician. The participants will be informed of the benefits and risks of the study in detail. After obtaining written informed consent, eligible participants will be randomly assigned to the experimental group and control group in a ratio of 1:1. To prevent design bias, we will follow the Consolidated Standards of Reporting Trials statement^[17]^ and the Standard Protocol Items: Recommendations for Interventional Trials (SPIRIT) 2013 statement.^[18]^ The study procedure is shown in Fig. 1 and the time points of the study is shown in Fig. 2.

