### Sample size

2.3

The calculation of sample size is based on the main results (6MWT). According to the previous literature,^[19]^ it is estimated that the average score of the control group was 442.5 and the standard deviation was 61.5. After Taiji Qigong exercise, the average of the experimental group was 486.7 and the standard deviation was 67.3. formula for calculating the sample size is as follows: 

At the 5% significance level, a total of 26 patients are needed in each group to achieve 80% power. The estimated dropout rate is 20%, and a total of 32 patients have been included in each group.

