### Outcome measures

3.4

The primary outcomes are the pulmonary function test (FEV_1_%, FEV_1_/FVC, and FVC) and 6-minute walking test (6MWT). The secondary outcome measures include blood gas parameters (PH, PaCO2, PaO2), the mMRC, Hospital Anxiety and Depression Scale (HADS), and St·George Respiratory Questionnaire (SGRQ). Baseline data will be collected before intervention. Outcome indicators will be collected at the 13th week.

The measurement of pulmonary function will be carried out by the same pulmonary function technician in the respiratory department. Before the test, the participants need to take a rest quietly for 10 minutes, then inhaled the bronchodilator salbutamol 200 μg. The arterial blood will be collected by the nurses in the department for blood gas analysis. 6MWT will be carried out by trained team members. Before the test, the participants need to take a rest for 10 minutes, and their blood pressure, pulse, and blood oxygen saturation will be measured. Carry a portable pedometer and walk as fast as possible. At the end of time, blood pressure, pulse, and blood oxygen saturation will be measured again, and the walking distance will be recorded. All the scales involved in this study will be completed by 3 specialized researchers who had received professional training and passed the examination.

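### The planned tests leave out the baseline values the trial collects and fix no primary test; ANCOVA would add precision, by an amount the documents do not let one state

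*Protocol article*

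**What the plan says.** Section 3.6 sets the method for continuous outcomes: "The measurement data will be examined using group *t* tests or non-parametric tests". It adds that "All statistical tests will be bilateral tests", with significance at P below .05. No baseline covariate is named. A normality condition appears in the same section, but it governs only how the data are described (mean and SD, or median and quartiles). That it also selects the test is a natural reading, not a stated rule.

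Section 3.4 says "Baseline data will be collected before intervention" and sets a single outcome assessment at week 13. It does not list which measures are taken at baseline, and the schedule figure is not shown. The primary outcomes are three lung-function measures and 6MWT.

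Section 2.3 bases the sample size on 6MWT: "it is estimated that the average score of the control group was 442.5 and the standard deviation was 61.5", and after exercise "the average of the experimental group was 486.7 and the standard deviation was 67.3". It concludes: "At the 5% significance level, a total of 26 patients are needed in each group to achieve 80% power". On attrition: "The estimated dropout rate is 20%, and a total of 32 patients have been included in each group".

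**The concern.** For a continuous outcome measured before and after treatment, adjusting for its own baseline removes the part of the outcome variance that baseline predicts, and it corrects the estimate for chance imbalance. The trial is small and the article mentions no stratification. If baseline 6MWT has an SD near 64 m (an assumption), the difference between arms at baseline has a standard error of about 18 m with 26 per arm, against a target effect of 44.2 m. An unadjusted comparison carries the predictable part of such a gap into the estimate.

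Leaving open a choice between a t test and a rank test also leaves the effect measure open until the data are seen. The trial is sized on a mean difference in metres, which a rank test does not estimate. With four primary measures, the choice could differ from one to the next.

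**Working it through.** **Inputs** (section 2.3, 6MWT): difference 486.7 − 442.5 = 44.2 m; SDs 61.5 and 67.3; 26 evaluable per arm. Allocation is 1:1 (section 2.1). Tests are two-sided at 5% (section 3.6).

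**1. The plan's own figure.** Common SD = √[(61.5² + 67.3²)/2] = √4155.8 = 64.47. Patients per arm for 80% power = 2(z₁ + z₂)² × SD²/difference².
- Two-sided: 2 × (1.960 + 0.842)² × 4155.8/1953.6 = 33.4, so 34 per arm (35 with the t distribution).
- One-sided: 2 × (1.645 + 0.842)² × 4155.8/1953.6 = 26.3, so 27 per arm.

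The stated 26 is not reproduced two-sided. It lies close to a one-sided calculation, which would conflict with section 3.6.

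**2. Power of the unadjusted t test.** Standard error = 64.47 × √(2/26) = 17.88 m. Noncentrality = 44.2/17.88 = 2.47 on 50 degrees of freedom. Power is 67.9% (69.6% by the normal approximation). With all 32 per arm evaluable it is 77.0%.

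**3. Power with ANCOVA.** The residual SD is 64.47 × √(1 − r²), where r is the baseline to week-13 correlation, with 49 degrees of freedom. The documents give no r, so the range is an assumption.

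| r | Residual SD (m) | SE (m) | Noncentrality | Power (t-based) |
|---|---|---|---|---|
| unadjusted | 64.5 | 17.9 | 2.47 | 67.9% |
| 0.2 | 63.2 | 17.5 | 2.52 | 69.6% |
| 0.3 | 61.5 | 17.1 | 2.59 | 71.9% |
| 0.4 | 59.1 | 16.4 | 2.70 | 75.3% |
| 0.5 | 55.8 | 15.5 | 2.85 | 79.9% |
| 0.6 | 51.6 | 14.3 | 3.09 | about 86% |
| 0.7 | 46.0 | 12.8 | 3.46 | 92.4% |

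Reaching 80% needs r of about 0.50.

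**4. Missing baseline walks.** If a fraction m of baselines is missing at random and replaced by the overall mean, the squared correlation falls to (1 − m)r². For illustration, r = 0.5 with m = 0.36 gives √(0.64 × 0.25) = 0.4, and power falls from about 80% to about 75%.

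**5. Cost of choosing the test by a normality check.** In 8,000 simulated trials with normal data at 26 per arm, power was 68.4% with the t test always, 68.2% with a Shapiro-Wilk check choosing the test, and 65.6% with the rank test always. Type I error with the check was 5.1%. The check costs about 0.2 points.

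**The case against.** A two-group t test after 1:1 randomisation is valid. Chance imbalance is already covered by its standard error, so it is not bias, and omitting a covariate is neither an error nor a contradiction. This stands: the issue is precision and prespecification. It could also be said that covariates belong in an analysis plan that is not shown. But section 3.6 is not silent. It names the tests, and the proposal replaces a stated method.

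Section 3.6 does not say whether the t test applies to week-13 values or to change from baseline, so baseline might enter through change scores. That would not be a substitute. The variance of change is 2(1 − r) times the raw variance. By the normal approximation, power for change at r = 0.3, 0.5 and 0.7 is 55.2%, 69.6% and 89.1%, against 73.6%, 81.5% and 93.3% for ANCOVA.

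Three stronger readings are tempting, and the documents do not support them.
- A reader might infer that adjustment restores 80% power. That needs r of about 0.5. Baseline falls in an acute exacerbation treated with NIV, and the Introduction reports poor compliance with getting out of bed, so a low correlation or missing walks are plausible.
- A reader might blame a normality check for lost power. The text ties normality only to description, and step 5 shows a negligible cost.
- A reader might trace the 68% to the analysis choice. It comes from the sample size: the same t test would have 80% power with 35 per arm.

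It also stands that section 3.4 does not name 6MWT among the baseline data.

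**Conclusion.** The point holds as one of efficiency and prespecification. The stated analysis is valid, but it omits baseline information and fixes neither the primary test nor the effect measure. For 6MWT at 26 evaluable per arm, ANCOVA would raise power from 68% to between about 70% (r = 0.2) and 92% (r = 0.7).

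The result rests on the protocol's means and SDs, an assumed correlation, and an observed baseline walk for nearly everyone. It covers 6MWT only, since the article gives no planning inputs for the three lung-function primaries. Adjustment may soften the shortfall in section 2.3, but it does not replace correcting that calculation.

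**What to change.** In section 3.6, state that week-13 6MWT is analysed by ANCOVA with treatment and baseline 6MWT, reporting the adjusted difference in metres with a 95% CI. Fix this in advance whatever the distribution looks like, with a rank test or robust standard errors as sensitivity analysis. Use the same model for FEV₁%, FEV₁/FVC, FVC, blood gases, HADS and SGRQ, each with its own baseline. Confirm in section 3.4 that these measures, including 6MWT, are taken at baseline. Keep participants without a baseline walk in the analysis through a prespecified imputed baseline. State the assumed correlation and show power over a range such as 0.2 to 0.7. Correct the sample size in section 2.3 separately.

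The cost is a paragraph of wording and a rule for missing baseline walks. The model is available in SPSS and, if 6MWT is indeed measured at baseline, needs no new data.
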